## Abstract

Multiple sclerosis (MS) is a chronic autoimmune disease characterized by inflammation, demyelination of axons, and oligodendrocyte loss in the central nervous system. This leads to neurological dysfunction, including hand impairment, which is prevalent among patients with MS. However, hand impairment is the least targeted area for neurorehabilitation studies. Therefore, this study proposes a novel approach to improve hand functions compared to current strategies. Studies have shown that learning new skills in the motor cortex (M1) can trigger the production of oligodendrocytes and myelin, which is a critical mechanism for neuroplasticity. Transcranial direct current stimulation (tDCS) has been used to enhance motor learning and function in human subjects. However, tDCS induces non-specific effects, and concurrent behavioral training has been found to optimize its benefits. Recent research indicates that applying tDCS during motor learning can have priming effects on the long-term potentiation mechanism and prolong the effects of motor training in health and disease. Therefore, this study aims to assess whether applying repeated tDCS during the learning of a new motor skill in M1 can be more effective in improving hand functions in patients with MS than current neurorehabilitation strategies. If this approach proves successful in improving hand functions in patients with MS, it could be adopted as a new approach to restore hand functions. Additionally, if the application of tDCS demonstrates an accumulative effect in improving hand functions in patients with MS, it could provide an adjunct intervention during rehabilitation for these patients. This study will contribute to the growing body of literature on the use of tDCS in neurorehabilitation and could have a significant impact on the quality of life of patients with MS.

## Introduction

1.

Multiple sclerosis (MS) is a chronic autoimmune disease that primarily affects females between the ages of 20 and 40 years old (1). Pathologically, it produces lesions throughout the central nervous system (CNS) in both gray and white matter (2) with demyelination of axons and oligodendrocyte loss and resulting neurological dysfunctions.

MS affects over 33,335 people in Australia (3) and more than two million worldwide (4). The neurological symptoms in these patients depend on the exact neuroanatomical location of these plaques. In the first year of the disease, the most reported symptoms are impaired sensory function (85%), fatigue (81%), impaired hand function (60%), and mobility (50%) (5). Among these symptoms, impaired hand functions were the least targeted area for neurorehabilitation studies (6) despite the fact that in a survey of 360 patients with MS, 88% of respondents rated hand and arm functions as being more important to them than lower limb functions (7). Johansson et al. (2007), reported that 167/219 patients with MS [Expanded Disability Status Scale (EDSS) range = 0–9.5] had a disability in their manual dexterity (8). In 2016, MS trust foundation in UK formally launched an awareness campaign “*Think Hand*” to increase the attention of medical professionals and drug manufacturers to hand and arm functions in this group of patients. This proposal is designed to take a step toward developing a ground-breaking approach to “restoring hand functions in patients with MS”.

## Motor learning, neuroplasticity and recovery post CNS injury

2.

Neuroplasticity can be defined as the ability of the brain to change, adapt and reorganize in a new environment (9) which is one of the main mechanism for restoration of motor skills e.g., manual dexterity post CNS injury. Motor skill learning can be considered as the acquisition of new patterns of muscle activation in time and space to improve performance of a motor task (10).

Motor learning consists of several phases. An initial rapid improvement (phase 1) is followed by a consolidation period that lasts several hours (phase 2), and then a slow learning phase which proceeds with continued practice and leads to gradual improvements in performance (retention—phase 3) (11). Phase 1 involves unmasking of connections by disinhibition (11), and changes in the strength of synapses driven by afferent feedback (11). Mechanisms behind the consolidation of synaptic plasticity (phase 2) include long-term potentiation (LTP) and long-term depression (LTD). The slow later stage (phase 3) may involve synaptogenesis and new functional connections (10). This learning-dependent plasticity plays an important role in functional recovery from CNS injury. LTP, LTD and formation of new synapses are all seen in M1, which is considered a crucial site for motor learning (10).

Myelin is the sheath that surrounds and insulates axons throughout the CNS, increases the speed of electrical communication among neurons and is synthesized by oligodendrocytes. It has been shown that in the adult brain, production of oligodendrocytes and myelin is a continuous process (12) which is necessary for learning new motor skills and also important for the process of neuroplasticity (13). McKenzie et al. (2014) showed the synthesis of new oligodendrocytes when mice were learning a new complex task. When the production of these cells was blocked before learning the task, the mice were not able to learn the task anymore. However, when the production of these cells was blocked after the learning process was completed, the mice still could recall the pre-learned task and complete the task with no problem (13). The researchers concluded that the generation of new oligodendrocytes is important for learning new motor skills. The structural changes in white matter were also shown in humans after practicing new motor skills such as playing piano (14) and juggling balls (15). MRI studies showed that activity-dependent myelo-modulation might underlie behavioural improvements by altering conduction velocity and synchronisation of nervous signals (16).

It has been argued that practicing a new motor skill triggers the formation of new neuronal connections or the strengthening of the existing connections in response to “repeating a particular sequence of movement”. The increased electrical activity in these circuits with practice will trigger the production of new oligodendrocytes and new myelination will make these connections stronger (17).

## Augmenting the use-dependent plasticity in M1 and motor learning consolidation by transcranial direct current stimulation

3.

Transcranial direct current stimulation (t-DCS) is a non-invasive technique that involves the application of weak, direct currents (1–2 mA) to the scalp via sponge-based rectangular pads (nominally 25–35 cm^2^) (18). This produces a sub-sensory level of electrical stimulation, which is imperceptible to most people during its application. In a small percentage of participants, it may cause minimal discomfort with a mild itching sensation, which usually disappears after a few minutes (19). The nature of these modulations depends on tDCS polarity. Using certain stimulation parameters, application of positive electrode (anode) over M1(a-tDCS) can increase; while application of negative electrode (cathode) over M1 (c-tDCS) can decrease the cortical excitability (20).

The immediate effect of tDCS occurs via altering ion concentrations in the extracellular space (21). However, pharmacological studies have revealed that the longer-lasting effects of tDCS are dependent on changes in neurotransmitter receptor function. There is an increasing body of evidence from pharmacological studies suggesting possible mechanisms contributing to the associated polarity-specific modulation of cortical plasticity. There is evidence for both GABAergic and dopaminergic modulation of tDCS-induced effects (22). Both the anodal facilitation and cathodal inhibition in M1 area are blocked by the N-methyl-d-aspartate (NMDA)-receptor antagonist dextromethorphan (20). Stagg et al. (2009) showed that facilitatory anodal stimulation leads to a significant decrease in the GABA concentration in the cortex. In contrast, inhibitory cathodal stimulation leads to a significant decrease in glutamate (23). It has been shown that co-application of neuropharmacologically active drugs may prolong or even reverse stimulation effects (20, 24).

TDCS-induced effects can be extended after the duration of stimulation by changing the efficacy of NMDA receptors (25). The long-term induced effects of tDCS may include formation of new synapses, which is necessary for the induction and maintenance of neuroplastic after-effect excitability enhancement by tDCS (25). These modulatory effects on cortical excitability, neurotransmitters and LTP mechanism are key elements for learning and memory processing which can be used for therapeutic purposes (26).

Over the past two decades, tDCS has been used as a neuromodulatory technique to enhance motor learning and motor functions in health and disease in human subjects (27). A-tDCS can be used as a stand-alone intervention (28) or as an add-on technique to prime the effects of other training methods (29). As tDCS induces a non-specific effect, it is generally agreed that a-tDCS-dependent behavioural gains can be optimized with concurrent behavioural training. Literature indicates that the application of tDCS during motor learning can have priming effects on the LTP-like mechanism of its action and prolong the effects of motor training in health and disease (30). This concurrent application of a-tDCS and motor training may also strengthen glutamate receptor learning-dependent activity, selectively boosting training-dependent activation of specific neural networks and promoting motor learning consolidation (31).

O'Brien et al. (2018) completed a systematic review and meta-analysis on the effect of a-tDCS on fine motor skills in patients after stroke (32). They examined the data of 351 stroke patients and showed moderate improvement of manual dexterity in this population when tDCS was applied alone and large improvement when it was concurrently applied with another intervention (32).

TDCS is a safe intervention with no or minimal side effects (19). However, the induced excitability changes and the length of lasting effect of tDCS strongly depend on the electrode montage and parameters of stimulation: *intensity* and *duration* of stimulation (33). The effects of a-tDCS can be prolonged by using higher intensities or by increasing the duration of its application. High-intensity stimulation can affect different neuronal populations compared with low intensity stimulation. By increasing the intensity, the current may reach deeper sites that might not be the intended target. It has been shown that longer application of a-tDCS may cause excitability diminution (34). This might be caused by a calcium overﬂow-caused neuronal counter-regulation (34). Therefore to increase the length of lasting effects, other characteristics of a-tDCS application should be considered. Within-session repetition of a-tDCS is another alternative for prolongation of the a-tDCS lasting effects. The efficacy of this technique has been already tested on healthy participants (35).

We are aiming (for the first time) to train patients to learn a completely new motor skill with their fingers rather than practicing the pre-injury well-learned tasks repeatedly to trigger the production of oligodendrocytes and myelin in the motor areas of their brain. We are also aiming to facilitate this learning process by combining the practice sessions with concurrent application of a-tDCS.

### Aim

3.1.

To assess whether applying within session repeated anodal transcranial direct current stimulation (a-tDCS) on primary motor cortex (M1) during learning of a new motor skill can improve hand functions in patients with MS more than conventional neuro-rehabilitation strategies for hand function improvement.

**Hypothesis 1:** Learning a new motor skill will be more effective in improving hand functions compared to the current hand training in patients with MS.

**Hypothesis 2:** In patients with MS, applying within-session repeated a-tDCS on M1 while learning a new motor skill for five days can improve hand functions more effectively than learning the new motor skill alone or with sham stimulation.

**Hypothesis 3:** As the protocol for within session repeated a-tDCS has accumulative and long-lasting effects on cortical excitability in M1 area, continuing hand training sessions during weeks 2–8 in the experimental group will be more effective in improving hand functions compared to patients in sham group or learning a new motor skill alone.

## Research plan

4.

### Design

4.1.

The is a randomized controlled trial.

### Participants

4.2.

Seventy two patients with secondary progressive MS will be recruited. These patients will be assessed by a rehabilitation physician against the inclusion and exclusion criteria. Eligible participants will then be enrolled in the study.

**Inclusion criteria: (**a) 18 years of age and over; (b) secondary progressive MS; (c) impaired dominant hand functions (right side); (d) EDSS = 3–6 and (e) able to understand, speak and write in English.

**Exclusion criteria:** (a) skin conditions (e.g., eczema, lesions) on scalp; (b) metal inside the head (outside the mouth) such as shrapnel, surgical clips, or fragments from welding or metalwork; (c) any implanted devices such as cardiac pacemaker, cochlear implant, medical pump, or intracardiac line; (d) frequent or severe headaches; (e) previous head injury and any other brain related disease and (f) pregnancy and breast feeding.

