### Experimental design

4.3.

Enrolled patients will be randomly allocated to one of four groups (*n* = 18 per group). Randomisation will be controlled by one of the investigators using a secure web-based computer-generated sequence which is a commonly used and reliable method for ensuring that study participants are assigned to different groups in a fair and unbiased manner (Figure 1).

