### A-tDCS intervention

4.5.

A DC-Stimulator (neuroConn. DC Stimulator plus) will be used to deliver 1 mA current to the M1 area via two surface electrodes with pockets of saline soaked sponges (0.9% NaCl). Active electrode (anode) measuring 3 × 4 cm will be placed over the left C3 or C4 according to the International 10–20 EEG system for electrode placement. The return (cathode) electrode (5 × 7) will be placed over contralateral supraorbital area. Participants will receive within-session repeated a-tDCS or sham tDCS paradigm (10-25-10 protocol) for 5 consecutive days. 10-25-10 protocol involves 10 min of tDCS intervention, followed by 25 min of rest, and then a further 10 min tDCS. The stimulator software has a study mode for blinding purposes that encodes sham and active stimulation parameters and can be set individually using the software. The safety and feasibility of this protocol and also its long-lasting effect in these patients have been assessed in our previous study (36).

#### Hand training session for group 1

4.5.1.

The patients in this group will be assessed by a physiotherapist and an individualized hand training program will be written based on the current practice standard.

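### The skin exclusion names only the scalp, while the return electrode sits on supraorbital skin, so forehead eczema or lesions do not exclude a patient as written

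*Protocol article*

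**What the plan says.** Section 4.2 (Participants) of the protocol article lists six exclusions, (a) to (f). Exclusion (a) is "skin conditions (e.g., eczema, lesions) on scalp". The other five deal with metal in the head, implanted devices, headaches, head injury or other brain disease, and pregnancy or breast feeding. None of them concerns skin. The same section says how the list is used: "These patients will be assessed by a rehabilitation physician against the inclusion and exclusion criteria".

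Section 4.5 (A-tDCS intervention) describes the stimulation. The device is to "deliver 1 mA current to the M1 area via two surface electrodes with pockets of saline soaked sponges". The two sites are then named separately: "Active electrode (anode) measuring 3 × 4 cm will be placed over the left C3 or C4", and "The return (cathode) electrode (5 × 7) will be placed over contralateral supraorbital area". The same paradigm, active or sham, runs on five consecutive days.

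Section 4.3 (Experimental design) sets the allocation: "Enrolled patients will be randomly allocated to one of four groups", with 18 patients in each. The group descriptions after it give active stimulation to Group 3 and sham to Group 4. Groups 1 and 2 have hand training only.

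**The concern.** The article does not explain exclusion (a). The natural reading of a scalp-skin exclusion in a stimulation trial is that it protects skin under an electrode. On that reading it should reach every place where an electrode is put. It reaches the anode site and stops there, although the article itself names a second site.

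What is at stake is mainly participant safety at one contact site. A physician who applies the list literally turns away a patient with eczema on the scalp and accepts one with the same condition on the forehead.

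Timing also matters a little. If a forehead condition is noticed only when the electrodes are fitted, that happens after randomisation and only in Groups 3 and 4. A criterion checked at screening applies to all four groups alike.

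**Working it through.** The article states no figure on this point, so there is none to reproduce. The check sets the exclusion list against the electrode sites, followed by simple proportions.

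**Step 1: sites against criterion.**

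| Contact site (section 4.5) | Anatomical location | Covered by exclusion (a), section 4.2? | Covered by (b) to (f)? |
|---|---|---|---|
| Anode, over C3 or C4 | Scalp | Yes | No |
| Return electrode, contralateral supraorbital | Forehead | No | No |

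The result does not depend on which hemisphere is stimulated, because the supraorbital area on either side is forehead. No other section adds a skin check at that site or widens the exclusion to the face or to electrode sites in general.

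**Step 2: does current reach the uncovered site?** Both electrodes belong to one circuit carrying 1 mA, so under active stimulation the same 1 mA passes through the forehead skin.

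**Step 3: who would be exposed?** Inputs are four groups of 18, 72 in total (section 4.3), with electrodes in Groups 3 and 4 and active current in Group 3. For one enrolled patient with a forehead skin condition:

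- chance of electrode placement on that skin: (18 + 18)/72 = 36/72 = 50%
- chance of active current through it: 18/72 = 25%
- chance of no electrodes: 36/72 = 50%

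These are chances for one such patient. Turning them into an expected number needs the frequency of forehead skin disease among candidates, which the article does not give.

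**Step 4: is electrode area a fair measure of the gap?** The article prints the return electrode as 5 × 7 without units; centimetres are assumed here.

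- anode: 3 × 4 = 12 cm², average current density 1/12 = 0.083 mA/cm²
- return electrode: 5 × 7 = 35 cm², average current density 1/35 = 0.029 mA/cm²
- ratio of densities: 12/35 = 0.34

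The uncovered site is the larger one, but its average current density is about one third of that at the covered site. Contact area should not be used as a measure of risk.

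**The case against.** The best defence is that the authors meant scalp loosely. Section 3, in its general description of the technique, speaks of current applied to the scalp through pads, in the plural. Read that way, exclusion (a) already means the skin under either electrode. This may well be the intention. It does not settle the matter, because section 3 is background, section 4.5 separates the two sites by name, and eligibility is judged on the list in section 4.2.

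A second defence is that a journal article condenses the full protocol, where electrode-site skin checks may be found, and that the safety and feasibility of the stimulation protocol were assessed in an earlier study by the same group. This would be decisive if the article were silent on skin. It is not silent: it states a skin rule and ties it to one of its own two contact sites. The earlier study bears on the stimulation protocol in general; the article does not say that it covered patients with forehead skin disease.

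Parts of the opposing case do stand, and they limit the point. A reader might infer any of the following, and the document supports none of them:

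- **That the two sections contradict each other.** Both can be followed at once. The criterion is narrower than the montage, which is a gap and not a conflict.
- **That every eligible patient with forehead eczema is stimulated through it.** Only those allocated to Group 3 receive active current.
- **That 36 patients each undergo repeated stimulation through unprotected skin.** Group 4 receives sham, and the figure of 36 counts everyone with electrodes, not those with forehead skin disease.
- **That the comparison of groups is biased**, because forehead irritation would reveal active stimulation or stop sessions mainly in Group 3. Nothing in the article shows this. It describes the stimulation as below the sensory level, with mild itching in a small percentage, and randomisation balances existing skin disease in expectation.

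**Conclusion.** The point holds as a gap in a stated eligibility rule. As written, the skin exclusion covers one of the two electrode sites, so a patient with eczema or lesions confined to the forehead can be enrolled and randomised to electrode placement on that skin.

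The conclusion rests on two readings: that the supraorbital area is not scalp, and that exclusion (a) is meant to protect skin under electrodes. The first is plain anatomy. The second is an inference, since the article gives no reason for the criterion.

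The correction is minor and concerns participant safety. The number of patients affected is unknown. Sample size, endpoints and analysis are untouched.

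**What to change.** Reconcile sections 4.2 and 4.5 so that the skin exclusion corresponds to the electrode sites the protocol names. If scalp was meant to include the supraorbital site, the criterion should say so. What counts as an excluding skin condition is for the sponsor and the clinical investigators to decide.

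Apply the reconciled criterion to all candidates at screening, before randomisation and whichever group they may enter, so that the four groups are drawn from the same eligible population.

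The cost is a few words in the exclusion list and an occasional extra screen failure. Some of those screened out would have been allocated to Groups 1 or 2 and never fitted with electrodes; that is the price of a single rule for all groups.

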### Experimental design

4.3.

Enrolled patients will be randomly allocated to one of four groups (*n* = 18 per group). Randomisation will be controlled by one of the investigators using a secure web-based computer-generated sequence which is a commonly used and reliable method for ensuring that study participants are assigned to different groups in a fair and unbiased manner (Figure 1).

**Figure 1 F1:**
[figure not shown]
Flow diagram of randomization, intervention and assessments. This figure shows the randomization of the participants into 4 groups and the allocated intervention and assessment sessions throughout the trial. MS: Multiple Sclerosis; tDCS: Transcranial direct current stimulation.

**Group 1: Control group** (*n* = 18): Patients in this group will participate in hand training sessions only based on the current standard in clinics for 8 weeks. During week 1 this will be provided in 5 sessions over 5 consecutive days (30 min with rest) and during weeks 2–8, participants will have 2 sessions per week. They will have the following assessments: baseline assessments (before training); assessments during hand training (week 1, at the end of 5 consecutive training sessions and end of week 2, 4, 6 and 8); and follow-up assessments (week 12).

**Group 2: Experimental group (Hand training only**) (*n* = 18): Patients in this group will participate in hand training sessions in the exact time frame as Group 1 but they will practice a new motor skill (Figure 2) during their hand training sessions. The time frame for the assessments will be exactly the same as for Group 1.

